### Cooperation

The study will be conducted in cooperation with the Cantonal Police Zurich (contact person, [name]), the University Hospital Zurich, which is the designated medical authority for the PPZ, and the Helsana AG (contact person, [name]). The Helsana AG is a major Swiss health insurance company with 2.1 million customers insured and will provide data on a matched Swiss cohort. Data will be extracted from the *Helsana Drug Report* [16], which is created in cooperation with the University Hospital Basel and the Institute for Pharmaceutical Medicine at the University of Basel. Another study site includes the University Hospital Zurich, Switzerland, which contractually provides all outpatient and inpatient medical care for the PPZ, including psychiatric consultations. No other parties are involved in the medical care of the PPZ prisoners.

### Data Collection and Management

Data entry into the health registry will be performed synchronously or asynchronously by a study team of physicians (TG, NM, PB, and MM) after carefully reviewing the source documents. A unique electronic case report form based on the variables in Table 1 and Table 2 was developed at the inception of this study. All source documents must be placed within the medical history of the prisoner. Table 1 and Table 2 summarize both the parameters and domains used in the study, which includes all variables, and other data extracted from the health registry. Unclear documentation will be discussed among the study team and incomplete data will be made apparent in the registry. After data entry, data will be checked for completeness and plausibility by the data manager. The database will be encrypted and only study personnel will have access to the source documents, which will not leave the prison. Encrypted backups of the database will be periodically conducted using external hard drives.

**Table 1 table1:** Summary table of the general domains and parameters, which will be part of the registry.

Domain, subcategories		Parameter	Comment
**General characteristics**			
	Age	Years	At baseline
	Sex	Male/Female	Self-reported
	Date of imprisonment	Date	Data obtained from police
	Length of imprisonment	Days (n)	Data obtained from police
	Country of origin	Sovereign state according to the United Nations	Data obtained from police
**Diagnosis**			
	Principal diagnosis	ICD^a^-10 code	German modification of the ICD
	Secondary diagnosis (up to 20)	ICD-10 code	German modification of the ICD
**Medication**			
	Medication according to external documents	Active agent, dosage, administration	With external verification of drugs with dispensing category “A+”^b^
	Daily medication	Active agent, dosage, administration	With external verification of drugs with dispensing category “A+”
	On-demand medication	Active agent, dosage, administration	With external verification of drugs with dispensing category “A+”

^a^ICD: International Classification of Diseases.

^b^Category A+ according to the Federal Act on Medicinal Products and Medical Devices (Therapeutic Products Act) Article 24 (eg, opioids, benzodiazepines, methylphenidate).

**Table 2 table2:** Summary of the systematic characteristics that will be assessed in the registry.

Characteristics, tests		Response	Explanation
**Particular characteristics at admission**			
	Reason for consulting a physician during the imprisonment	Text	Self-reported
	Evidence of a traumatic injury at admission	Yes/No	If applicable, then nature of the injury
	Need for a “Hafterstehungsfähigkeit”^a^	Yes/No	Data obtained from police
	History of illicit drug abuse	Yes/No	Data obtained from police
	Participant in the opioid replacement therapy program	Yes/No	Data obtained from police
	History of benzodiazepine dependence	Yes/No	Data obtained from police
	History of alcohol dependence	Yes/No	According to the DSM-IV^b^ criteria
	Result of the alcohol breath test at admission	mg/L	Optional
	Evidence of body packing (according to computed tomography scan results)	Yes/No	Data obtained from hospital
**Particular characteristics during the imprisonment**			
	Need to consult a psychiatrist during imprisonment	Yes/No	Data obtained from police
	Admission to a hospital during imprisonment	Yes/No	Data obtained from police
**Special reports**			
	Blood pressure chart	Source document	Optional
	Blood sugar chart	Source document	Optional
**Medical history**			
	External documents	Source document	Optional
	Laboratory results (including pregnancy test)	Source document	Optional

^a^Hafterstehungsfähigkeit: initial 24/7 medical assessment by a physician, after which it is decided whether the convict can be admitted to the prison in the first place.

^b^DSM-IV: Diagnostic and Statistical Manual of Mental Disorders, Fourth Edition.

### Quality Control

For this health registry, the following 4 quality control measurements will be implemented, and the results will be provided in the final manuscript:

Interobserver variability: The source documentation of 150 random patients will be processed by 2 physicians (ie, 450 degrees of freedom for every variable will be assessed) and disparities observed with regard to all domains will be summarized.Matching with a local database from the jurisdiction: Data from the health registry will be compared with data from the jurisdiction, and discrepancies (eg, country of origin) will be further investigated by the study team.Internal validity: The consumption of medications will be summarized for each month from 2015 to 2020, and these data will be compared with the prescription data collected from the PPZ’s local pharmacy, which collects monthly data for all dispensed medications. This step ensures that the actually dispensed medication is equal to the prescribed medication.Verification of the source documents: Foreign health-related documents must be checked and, if necessary, translated to German by a recognized body (eg, translation services). In case of an already established course of pharmaceutical drug treatment with the dispensing category “A+,” according to the Federal Act on Medicinal Products and Medical Devices (Therapeutic Products Act) Article 24 (eg, opioids, benzodiazepines, methylphenidate), they require an external verification of the original prescription and a statement from the physician. Written verifications by the federal authorities or nongovernmental organizations involved in the opioid replacement therapy program will also be accepted. Other verifications by nongovernmental organizations (eg, refugee organizations) will not be accepted.

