**Methods:**

Demographic and health-related data such as age, sex, country of origin, duration of imprisonment, medication (including the drug name, brand, dosage, and release), and medical history (including the International Classification of Diseases-10 codes [German modification] for all diagnoses and external results that are part of the medical history in the prison) have been deposited in a central register over a span of 5 years (January 2015 to August 2020). The final cohort is expected to comprise approximately 50,000 to 60,000 prisoners from the Police Prison Zurich, Switzerland.

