### Participants

This study consists of prisoners within the PPZ from April 1, 2015 until August 31, 2020. The final sample will be exhaustive. All inmates within this timeframe will be included in this study and there will be no random selection. Only in documented cases wherein a prisoner allegedly refuses to participate in health-related activities, he or she will be excluded from the study and his or her data will not be analyzed. Otherwise, there are no exclusion criteria. Extrapolating from current numbers (approximately 850 prisoners per month × 64 months), it is expected that the final database will contain data from approximately 50,000 to 60,000 prisoners.

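### The monthly pharmacy comparison is an aggregate plausibility check and cannot ensure that dispensed medication equals prescribed medication

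*Protocol article*

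**What the plan says.** The protocol article (Methods, Quality Control) lists four measures whose results will appear in the final manuscript. The third, labelled internal validity, has two sides.

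- Registry side: "The consumption of medications will be summarized for each month from 2015 to 2020".
- Pharmacy side: "prescription data collected from the PPZ’s local pharmacy, which collects monthly data for all dispensed medications".

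The stated conclusion is: "This step ensures that the actually dispensed medication is equal to the prescribed medication".

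Table 1 has three medication fields: medication from external documents, daily medication, and "On-demand medication". Each is recorded as "Active agent, dosage, administration". Table 1 also holds the date of imprisonment and "Length of imprisonment" in days. The Data Collection and Management section presents Tables 1 and 2 as covering all registry variables. The Abstract describes the medication data differently, as "medication (including the drug name, brand, dosage, and release".

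**The concern.** The sentence claims a property that the described comparison does not have. There are three reasons.

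1. Both sides are monthly summaries, and no linkage to individual prisoners is described. Agreement between summaries is compatible with many wrong individual records.
2. A comparison can detect a difference. It cannot ensure that none exists. No tolerance and no action on a mismatch are given for this step, whereas the check against the jurisdiction's database says that discrepancies will be followed up.
3. The text moves between consumption, prescription and dispensing, and uses the last two for the same pharmacy source. The registry fields describe ordered drug, so the reader cannot tell which two quantities are compared.

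What is at stake is what the manuscript may say about its medication data. These data bear on the second hypothesis, on off-label drug use, and the external comparison data are drawn from an insurer's drug report. A good monthly match, reported under this wording, would be read as proof that individual medication records are correct.

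**Working it through.** The plan attaches no figure, tolerance or error rate to this check, so there is nothing to reproduce. The check is a reading of the fields followed by an illustration on assumed rates.

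**What the fields can yield**

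| Quantity | Available from the listed fields? |
|---|---|
| Ordered daily dose | Yes (dosage of daily medication) |
| Days in the prison, and their calendar placement | Yes (length and date of imprisonment) |
| Start and stop of a drug within the stay | Not listed |
| Doses given or taken | Not listed |
| On-demand doses taken | Not listed |
| Quantity dispensed | Pharmacy only |

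For daily medication, an expected quantity for agent *a* in month *m* can be formed as the sum over inmates of dosage × days of stay falling in *m*. This is prescribed drug, and it assumes treatment throughout the stay. No such proxy exists for on-demand drugs. Drugs known only from external documents need not have been dispensed in the prison.

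**Exact offset**

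Take 100 dispensed courses, of which 10 are not recorded, and add 10 recorded courses that were never dispensed. The registry holds 100 − 10 + 10 = 100 courses, and the ratio is 100/100 = 1.00. Yet 10 of 100 registry courses are false and 10 of 100 dispensed courses are missing. Swapping equal quantities between two inmates likewise changes the total by 0.

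**Random offset**

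- From the documents: about 850 prisoners per month (Participants), about a third needing medical attention, and a maximum stay of 7 days (Study Site). 850/3 ≈ 283.
- Assumed: all 283 receive one unit per day; stays are uniform on 1 to 7 days; a share *e* of inmates is recorded one unit per day too high or too low, with equal chance.

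Mean stay is 4 days, so the monthly total is about 283 × 4 = 1,132 units. The mean squared stay is (1+4+9+16+25+36+49)/7 = 20. The net error has mean 0 and SD √(283 × *e* × 20). For *e* = 0.10 this is √566 = 23.8 units, or 23.8/1,132 = 2.1% of the total. The median absolute net error is about 0.674 × 2.1% = 1.4%. A simulation of 20,000 months under the same assumptions gives:

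| Inmates in error | Mean gross error, % of units | Median net difference in total | 95th percentile of net difference | Months agreeing within 2% |
|---|---|---|---|---|
| 5% | 5% | 1.0% | 2.9% | 83% |
| 10% | 10% | 1.4% | 4.1% | 66% |
| 20% | 20% | 2.0% | 5.8% | 50% |

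With a fifth of inmates misrecorded, half the months would still agree within 2%.

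**What the check can see**

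If the 10% of errors were all omissions, the expected gap would be 0.10 × 1,132 ≈ 113 units, or 10% of the total, in every month. That is well outside the random spread above, so systematic under- or over-recording is detectable.

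**The case against.** The strongest reply is that only one verb is too strong and little depends on it. Much of this stands.

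- **Other checks exist.** A reader might infer that this step is the only evidence for the medication data. It is not. The interobserver review has two physicians process the records of 150 random patients across all domains, which include medication, and category A+ drugs need external verification. Neither sets the registry against dispensing, so this step is unique only in that respect.
- **A proxy exists.** A reader might infer that the registry cannot yield consumption at all. For daily medication, dosage times length of stay gives an approximate expected quantity. The limitation is that this measures prescribed drug, and nothing comparable is available on demand.
- **On-demand handling is not stated.** One can construct a large mismatch: a drug allowed 4 times daily over 3 days, counted as 4 × 3 = 12 units when 3 were taken, would be overstated 4-fold. The protocol does not say that on-demand drugs will be counted this way, so this is a risk left open and not a described error. The article may also leave such detail to a fuller document.
- **Refusers.** For documented refusers the plan states that "he or she will be excluded from the study and his or her data will not be analyzed", while the pharmacy data cover everything dispensed. The documents give no number of refusers, and people who refuse health-related activities may receive little medication. No size can be claimed.
- **Brand and release.** Their absence from Table 1 rules out matching by product but not by active agent.
- **Aggregation is inferred.** The text speaks of monthly summaries and never of totals. Aggregation is the natural reading, since the pharmacy data are described as monthly and no patient linkage is mentioned.
- **The error rates are assumed.** The documents give none, and equal chances of over- and under-recording favour cancellation.

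None of this rescues the claim. Comparing monthly summaries cannot ensure equality, and a fuller document could add detail without making the published sentence true.

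**Conclusion.** The concern holds in this limited form. The step is a useful aggregate plausibility check that can reveal systematic gaps. It does not establish that dispensed equals prescribed medication for individuals, and the listed fields do not measure consumption. The percentages in the illustration depend on the assumed error rates, symmetric errors, uniform stays, one unit per day, and treating everyone who needs medical attention as medicated. The qualitative conclusion needs only that errors can go in both directions.

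The consequence is confined to what may be concluded about medication data. The primary outcome and both listed secondary outcomes are ICD-10 prevalence measures, and none depends on this check. The Abstract and Table 1 also disagree on whether brand and release are recorded. That is a smaller matter, to be settled at the same time.

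**What to change.** 1. Replace the claim that equality is ensured. Describe the step as an aggregate plausibility check that can reveal systematic differences between registry and pharmacy but gives no evidence of agreement for individuals.
2. State what each source measures: prescribed quantity in the registry, dispensed quantity in the pharmacy. Drop the terms consumption and prescription data where they do not apply.
3. Run the check per active agent and calendar month. The registry side is the expected quantity of daily medication, dosage × length of imprisonment, placed by date of imprisonment. The pharmacy side is the dispensed quantity in the same unit.
4. Leave external-document medication out of the comparison. Tabulate on-demand medication separately, because doses taken are not recorded.
5. Report the registry-to-pharmacy ratio for each agent and month. Note that the pharmacy figure may include excluded refusers and that the registry figure assumes treatment for the whole stay.
6. Reconcile the Abstract with Table 1: either add brand and release to the case report form, or remove them from the Abstract and keep the comparison at active-agent level.

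The cost is a weaker quality claim, some changed wording and a slightly longer tabulation from fields already planned. Adding brand and release is optional and would cost two fields.

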### Data Protection

In this registry, anonymized health data will be analyzed and stored. Other sensitive data, particularly, religious, political, social security, or administrative data will not be included as part of this study. The anonymized data sets generated or analyzed during this study will be available upon request from TG. Data are handled according to the Schengen Data Protection Act.

### Statistical Considerations

Statistical analyses will be conducted by the study team in consultation with senior statisticians. For baseline analyses, means or medians will be reported according to the distribution of the continuous variable. Proportions will be reported for categorical variables. For hypothesis testing, a two-sided *t* test for normally distributed continuous variables and nonparametric tests for nonnormally distributed continuous variables will be conducted; chi-square testing will be used for categorical variables. Linear or logistic regression models with or without adjustment for potential confounders (ie, age, sex, nationality) will be used when appropriate. Regression analysis estimates will be reported using 95% confidence intervals, and a two-sided *P* value of <.05 will be considered statistically significant for all reported tests. For the longitudinal data, a generalized linear mixed model with random effects (accounting for the nationality of the prisoner during the refugee crisis) will be used when appropriate. Statistical analyses will be performed using STATA Version 16 (StataCorp LP).

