### Hypothesis

In summary, the prison population is very vulnerable; yet, hardly any reliable data are available on the health of inmates [1,3]. The current geopolitical situation appears to exacerbate the problem as patients with a disproportionately poor health status have contact with the Swiss health care system. Data from the PPZ offer a unique opportunity globally for a representative analysis of the disease profile of inmates. The aim of this study is to collect health-related data in order to give insight into an unexplored area and underserved patient population. First, we hypothesize that the disease profile of inmates substantially differs from that of the general population. Specifically, certain chronic and psychiatric diseases are disproportionately prevalent among inmates and refugees. Second, a large number of drugs (eg, NPS) may be used “off-label,” and the origin of the inmates and the refugee route may have an impact on the disease profile of the affected. Third, recent geopolitical changes have significantly affected the overall disease profile of inmates.

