### Outcomes

The primary outcome measure will be disease prevalence by using cross-sectional data from prisoner’s medical records (ie, using the ICD-10 codes [German modification]) from 2015 to 2020. Secondary outcome measures include the following: (1) A comparison of disease prevalence (ICD-10 codes [German modification]) of the inmates at the PPZ to that of a representative sample from the local resident population by using cross-sectional medical records from all inmates at the PPZ from 2015 to 2020 and (2) longitudinal changes in disease prevalence (ICD-10 codes [German modification]) from 2015 to 2020 by using cross-sectional medical records from all inmates at the PPZ.

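### The model for change from 2015 to 2020 names nationality as its only grouping factor, so its P values can be too small for commoner diagnoses if prevalence varies between calendar months beyond binomial noise

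*Protocol article*

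**What the plan says.** The second secondary outcome is "longitudinal changes in disease prevalence (ICD-10 codes [German modification]) from 2015 to 2020 by using cross-sectional medical records from all inmates at the PPZ" (Outcomes). The third hypothesis is that "recent geopolitical changes have significantly affected the overall disease profile of inmates" (Hypothesis). For such data, Statistical Considerations states that "a generalized linear mixed model with random effects (accounting for the nationality of the prisoner during the refugee crisis) will be used when appropriate". The same section says that "chi-square testing will be used for categorical variables", lists logistic regression with possible adjustment for age, sex and nationality, and adds that "a two-sided *P* value of <.05 will be considered statistically significant for all reported tests". It names no random effect, clustered standard error or overdispersion term for month, season or year.

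The Participants section gives the window: "This study consists of prisoners within the PPZ from April 1, 2015 until August 31, 2020". It derives the sample size from "approximately 850 prisoners per month × 64 months". Table 1 already records "Date of imprisonment" for each inmate.

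**The concern.** Calendar time is the exposure in this comparison. Stays last at most seven days, so each month brings largely new inmates to a single site. People admitted in the same month can share influences such as an outbreak, a police operation or a staffing change. The conditions of interest under Study Questions include scabies, traumatic injuries and body packing, for which such shared variation is plausible.

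A nationality intercept is common to inmates of one nationality across all months, so it does not represent a disturbance common to all nationalities in one month. Fitted as named, the model's null hypothesis allows only binomial variation around a constant prevalence within nationality. Any further month-to-month variation is missing from the standard error of the time effect. At stake are false claims that a diagnosis became more or less common over the period, in results meant for policymakers. A multiplicity correction would not repair this, because each single P value would already be too small.

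**Working it through.** **The plan's own figure.** 850 × 64 = 54,400, inside the stated 50,000 to 60,000. April 2015 to August 2020 is 9 + 4 × 12 + 8 = 65 months, and 850 × 65 = 55,250. The difference is immaterial here. The article states no error rate for the change test beyond the nominal two-sided 5%.

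**Inputs.**
- From the article: m = 850 admissions per month (Participants). About a third of inmates need medical attention (Study Site), so m ≈ 850/3 ≈ 283 if only those are analysed.
- Assumed, because the article gives neither: prevalence p, and the between-month SD s on the logit scale.

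**Formula.** The binomial variance of one month's log-odds is about 1/[m p(1−p)]. Independent month effects add s². The ratio of true to modelled variance is DE = 1 + m p(1−p)s². The actual type I error is 2[1 − Φ(1.96/√DE)].

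**Example.** With m = 850, p = 0.10 and s = 0.10: DE = 1 + 850 × 0.09 × 0.01 = 1.765, √DE = 1.329, 1.96/1.329 = 1.475, and the error is 0.14.

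| m | p | s = 0.05 | s = 0.10 | s = 0.20 |
|---|---|---|---|---|
| 850 | 1% | 0.052 | 0.060 | 0.090 |
| 850 | 5% | 0.062 | 0.098 | 0.226 |
| 850 | 10% | 0.073 | 0.140 | 0.331 |
| 850 | 20% | 0.090 | 0.202 | 0.440 |
| 283 | 1% | 0.051 | 0.053 | 0.063 |
| 283 | 10% | 0.057 | 0.080 | 0.168 |

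At s = 0 the error is 0.05 throughout. DE does not contain the number of months, so a long study period does not cure the problem. In the rows for 283, p is the prevalence among those seen.

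**Simulation check.** Settings: 65 months, 10 nationality groups with intercept SD 0.4, no true trend, independent month effects and 1,500 runs per setting. Nationality was fitted as stratum intercepts, standing in for the random intercept. Results at m = 850 and p = 10%:

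| Test | s = 0 | s = 0.10 | s = 0.20 |
|---|---|---|---|
| Trend, nationality modelled, month ignored | 0.048 | 0.123 | 0.338 |
| Chi-square, April–December 2015 v January–August 2020 | 0.035 | 0.145 | 0.313 |
| Trend, month-clustered standard error, t reference | 0.053 | 0.051 | 0.060 |

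Over all 18 settings run (m = 850 or 283; p = 5%, 10% or 20%; s = 0, 0.10 or 0.20), the month-clustered test stayed between 0.046 and 0.060.

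**The case against.** The strongest reply is that this is a condensed article. It speaks of random effects in the plural, makes their use conditional, and does not say that nationality is the only one. It does not state how time enters the model. Nationality is also tied to the refugee crisis, which could mean a nationality-by-period effect that the simulation does not represent. A reader might infer that the plan rules out a time effect; the text does not support that. What remains is that the article chose to name a grouping factor for the longitudinal data, and the one named does not address the error relevant to a time contrast. The conditional wording also leaves open a fallback to unclustered tests with the same weakness.

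A second reply is that the sample is exhaustive, so a shift caused by an outbreak is a real change in who was ill at this prison. That holds for pure description. It fits poorly with P values, and worse with a hypothesis that attributes change to geopolitics. A month effect does not settle that attribution either.

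Third, many ICD-10 codes will be rare, and for those the excess is small. High prevalences among all inmates may also be unrealistic: if diagnoses come only from the third who are seen, 20% of all inmates is 0.20 × 850 = 170 of 283, or 60% of those seen.

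Fourth, the 2015-versus-2020 wording stands in the objective that compares inmates with residents. It should not be assumed that a two-year contrast among inmates is planned.

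Finally, the simulated repair assumes independent months. Season and disturbances lasting several months need separate handling. This stands, and the fix allows for it.

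**Conclusion.** The point holds conditionally. If the model is fitted with nationality as its only grouping factor, and months vary beyond binomial noise, the test of change is anti-conservative. With 850 admissions per month and 10% prevalence, the error is about 7%, 14% and 33% for an SD of 0.05, 0.10 and 0.20. At 1% prevalence it is about 5%, 6% and 9%. If only the third needing care is analysed, it is about 8% and 17% at 10% prevalence for an SD of 0.10 and 0.20. These figures rest on assumed prevalences, assumed SDs and independent month effects.

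A reader might infer that ordinary chance swings will be declared significant too often. The article does not support that. Pure sampling variation is already in the binomial variance, and whether extra variation exists, and how large it is, cannot be learned from the text. The point concerns one secondary outcome and the third hypothesis, not the overall prevalence estimates.

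**What to change.** In Statistical Considerations, extend the longitudinal model as follows:

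- Add a random intercept for calendar month of admission, derived from the date of imprisonment and crossed with nationality. Alternatively, use standard errors clustered by month with a small-sample t reference based on the number of months.
- Include a season term. Under the Participants window, 2015 contributes April to December and 2020 contributes January to August.
- Check residual autocorrelation between months, since an independent month effect does not cover disturbances that persist.
- Use this model, not an unclustered chi-square or logistic test, for the 2015–2020 trend and for any 2015-versus-2020 contrast among inmates. Report the between-month SD for each diagnosis.

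The change takes a few sentences and somewhat more model fitting, and needs no new data. The price is wider intervals and fewer significant changes. If months do not vary, the estimated month variance should be near zero and little is lost.
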